# A randomized controlled trial to evaluate the effectiveness of a staff training program to implement consumer directed care on resident quality of life in residential aged care

**DOI:** 10.1186/s12877-018-0966-1

**Published:** 2018-11-23

**Keywords:** Consumer directed care, Staff training, Resident quality of life, Residential aged care, Resident choice and control

## Abstract

**Background:**

Residential Aged Care Facilities (RACFs) are moving towards a Consumer Directed Care (CDC) model of care. There are limited examples of CDC in ageing research, and no evaluation of a comprehensive CDC intervention in residential care was located. This study will implement and evaluate a staff training program, Resident at the Center of Care (RCC), designed to facilitate and drive CDC in residential care.

**Methods:**

The study will adopt a cluster randomized controlled design with 39 facilities randomly allocated to one of three conditions: delivery of the RCC program plus additional organizational support, delivery of the program without additional support, and care as usual. A total of 834 staff (22 in each facility, half senior, half general staff) as well as 744 residents (20 in each facility) will be recruited to participate in the study. The RCC program comprises five sessions spread over nine weeks: Session 1 clarifies CDC principles; Sessions 2 to 5 focus on skills to build and maintain working relationships with residents, as well as identifying organizational barriers and facilitators regarding the implementation of CDC. The primary outcome measure is resident quality of life. Secondary outcome measures are resident measures of choice and control, the working relationship between resident and staff; staff reports of transformational leadership, job satisfaction, intention to quit, experience of CDC, work role stress, organizational climate, and organizational readiness for change. All measures will be completed at four time points: pre-intervention, 3-months, 6-months, and 12-month follow-up. Primary analyses will be conducted on an intention to treat basis. Outcomes for the three conditions will be compared with multilevel linear regression modelling.

**Discussion:**

The RCC program is designed to improve the knowledge and skills of staff and encourage transformational leadership and organizational change that supports implementation of CDC. The overarching goal is to improve the quality of life and care of older people living in residential care.

**Trial registration:**

ACTRN12618000779279; Registered 9 May 2018 with the Australian and New Zealand Clinical Trials Registry (ANZCTR; http://www.anzctr.org.au/).

## Background

The residential aged care system in Australia and internationally is striving towards a Consumer Directed Care (CDC) model, an approach to resident care that emphasizes consumer choice and control. This model of care places the residents at the center of care, such that the residents have choice and control over their care and activities. CDC is designed to improve the residents’ quality of life (QoL) by supporting them in directing the design and delivery of the services they receive [1]. Introducing CDC will require Residential Aged Care Facilities (RACFs) to move away from a traditional approach to care, which is typically driven by the routines and efficiencies of the organization [2]. RACFs will need to adapt this prevailing mindset and logistics in order to support the dignity, autonomy, and independence of residents [3] and more comprehensively meet individual resident care preferences. There are currently considerable gaps in our knowledge of how to achieve and sustain this model of care. Research on implementation and efficacy of CDC is limited, with most published CDC studies focusing on its delivery in community aged care [4, 5]. While person-centered approaches have been evaluated in the aged care context with some positive outcomes [6, 7], no specific CDC-based staff training programs have been evaluated in RACFs. Our project will address this gap by providing an innovative approach to RACF staff training so that they can effectively implement CDC in residential care.

Challenges associated with implementing a resident-directed approach in aged care include the lack of staff empowerment to handle the shift towards CDC philosophy, the need for substantial job restructuring, resistance to change, and the need for strong leadership to support practice change [8, 9]. Implementing a CDC approach therefore requires training the care staff and facility management in CDC strategies (for example, implementing resident choice and control regarding activities and daily routines) as well as focusing on change management and leadership strategies. In particular, a transformational style of leadership is central to translating the knowledge and skills relevant to CDC into practice. Transformational leaders are focused on change [10], and are able to bring about awareness and acceptance of mission and purpose within the organization that results in a wide variety of positive outcomes [11]. As such, they are more likely to engage and generate positive attitudes about the required organizational change among care staff when compared to non-transformational leaders [8, 12].

The organizational climate is critical to translating the CDC strategies into practice. A fundamental change in how a RACF functions under CDC is the focus on each resident’s participation in the planning and delivery of the services they receive, as opposed to the efficiency of care delivery. Thus the focus is on reorganizing the activities of the facility to address the expressed needs of the residents, rather than being focused on tasks identified by facility staff. Aspects of organizational change and staff relationships, such as role clarity and innovation [13], work pressures, commitment and trust, will be essential to this shift. Our previous work with 255 aged care workers across 21 RACFs demonstrated that, in addition to transformational leadership, work pressure and innovation were predictive of aged care employees’ perceptions of organizational readiness for change [14]. Work pressure may be predictive of readiness for change if workers perceive that the change will alleviate pressure [14], while innovation indicates that the organization encourages change and creativity [15]. It is important to examine the role of all of the factors as they relate to the implementation of CDC.

Beyond organizational factors, working relationships between RACF care staff and residents are likely to be central to the success of CDC and improvement of resident QoL. Positive interactions between staff and residents can build trust and give residents a sense of respect and acknowledgment, which, in turn, can be the foundation for the ongoing collaboration needed to support residents’ involvement in their care [16]. Additionally, meaningful relationships, as determined from both the resident and staff perspectives, are expected to improve both resident quality of life [17] and staff job satisfaction [12, 18].

Our Resident at the Center of Care (RCC) training program consists of five sessions and is directed at managers and general staff. It has been developed to address the critical factors outlined below (transformational leadership, organizational climate, and the working relationship between staff and residents) in order to drive real and sustainable change in implementing and embedding CDC in residential aged care, and so improve resident QoL. Education (training) alone is necessary but insufficient for driving practice change [19]. Further, large scale reforms like CDC are disruptive to existing practice and likely to be viewed ambivalently by staff [20]. It is therefore important to embed knowledge translation strategies into the RCC program to enable change.

### Hypotheses and expected outcomes

It is hypothesized that, relative to care as usual, the RCC Program will improve residents’ QoL (Primary Outcome Measure – QoL at 6-months follow-up); their perceptions of their level of choice and control and the working relationship with staff (Secondary Outcome Measures). It is also hypothesized that the RCC Program will lead to organizational change; improve staff perceptions of their use of transformational leadership, job satisfactions, working relationship with residents, experience of CDC; reduce their job stress and intention to quit (Secondary Outcome Measures). Supplementing the RCC Program with extra support to assist staff to address barriers to CDC implementation and so implement change is hypothesized to lead to greater benefits than the same program without this support. These changes are predicted to occur, relative to baseline at 3-months, 6-months, and 12-months follow-up.

## Methods/design

### Study design

A cluster randomized controlled trial design will be employed in this study, with 39 facilities randomly allocated to one of three conditions (13 facilities in each). Each of the 13 aged care organizations will provide three separate facilities to take part in the study, which will then be randomly allocated to one of the three conditions. Allocations of facilities will be completed by the biostatistician not involved in data collection using random numbers generated at random.org.

The first condition will involve the delivery of the five-session RCC Program plus additional organizational support. This organizational support is designed to assist staff to implement the CDC model of care within their facility. It will be provided one day a week for four weeks following Session 3 and a further one day a week for 12 weeks following Session 5. This training is above and beyond what is provided within each session of the training program, and is designed to assist staff in applying their learnings from the program (in line with the facility’s CDC implementation plan) and assist the staff to work through challenges as they arise. Sessions 4 and 5 will occur immediately after a four-week gap (see Fig. 1). The second condition will be a second intervention group, where staff will be provided with the RCC Program without the additional organizational support. The third condition will be a ‘care as usual’ control group. Staff will be provided with paid release time to attend the program. Data from the residents will be collected by a research assistant who is blind to the condition to which the facility is allocated.

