**Fig. 1 Fig1:**
[figure not shown]
Flow chart of staff recruitment, baseline, roll out of the program, post-intervention and follow-up

A 0.5 FTE study champion appointment will be made by each organization. This study champion will be recruited from the commencement of the study, with a brief to work with staff and the research team to assist in the roll out of the strategies identified as a result of the training program. This study champion will assist in the recruitment of staff and residents for the study as well as assist staff to embed the strategies from the program into routine practice. The study champion will be an important link between the staff in the two intervention facilities and the research team implementing the protocol. In addition to the organizational support provided for Condition 1, the study champion will assist staff to overcome barriers to CDC implementation throughout the 15 months of the study period. The overall study will run from January 2018 through to December 2020. The first round of staff and resident recruitment and data collection commenced in May 2018 and it is anticipated the final round of data collection will be completed by July 2020. The roll-out of the training program will run from June 2018 to July 2019. The second half of 2020 will be dedicated to data analysis and interpretation, and writing of publications.

Informed by the results of our earlier NHMRC-funded RCT (APP1042156) our study is designed to detect a moderately small difference *d* ≥ 0.35 between the RCC plus organizational support and control Condition in QoL of residents at 6-months follow up (primary outcome) and in staff outcomes post-intervention (secondary outcomes). We selected 6-months follow up as our primary endpoint for residents’ QoL because we expect a gradual and continuing change in this outcome as a result of changing practice. Allowing for 80% power, 5% Type I error rate (2-tailed), intra-class correlation of 0.02 for the within-facility clustering, and 25% (residents) and 33% (staff) attrition over time, we will need to randomize at least 744 residents (248 per Condition) and 834 staff (278 per Condition). Based on our previous work in the residential aged care setting, we expect an average recruitment of 20 residents and 22 staff per site. Hence, 39 aged care facilities will need to be enrolled into the study (13 for each arm of the RCT). Data analysis is discussed later in the Methods/Design section.

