### Statistical analysis

Primary analyses will be on an intention to treat basis, with supplementary ‘per protocol’ analyses (at least 75% of staff enrolled in the study completing at least 75% of training sessions). To account for the within-facility clustering and repeated assessments of staff and residents, hypothesized main effects for outcomes will be tested using a multilevel linear (or generalized linear, where appropriate) regression modelling. For each outcome, a separate three-level regression model will be specified, with repeated measurements as level 1, individuals as level 2, and facility as level 3. The regression models will include Condition allocation, assessment time point, and Condition by time interaction as predictors. Facilities and individuals will be modelled as random effects with remaining variables modelled as fixed effects. Missing data will be handled with conditional maximum likelihood estimation. The impact of possible non-random attrition will be explored with simulation analyses.

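### Facilities are randomised within organisations but the planned model has no organisation term, so the 6-month comparison between conditions is conservative to the extent that organisations differ

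*Protocol article*

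**What the plan says.** On allocation, the Study design section has "39 facilities randomly allocated to one of three conditions (13 facilities in each"), and adds: "Each of the 13 aged care organizations will provide three separate facilities to take part in the study, which will then be randomly allocated" to a condition. Later in the same section, after Fig. 1, "A 0.5 FTE study champion appointment will be made by each organization", and this person is "an important link between the staff in the two intervention facilities and the research team". Two intervention facilities out of an organisation's three leave one control facility. The article never writes out that each organisation has exactly one facility per condition, but these statements fit that reading and hardly any other.

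On analysis, the Statistical analysis section sets up a three-level regression for each outcome, "with repeated measurements as level 1, individuals as level 2, and facility as level 3". The terms are listed: "The regression models will include Condition allocation, assessment time point, and Condition by time interaction as predictors". The random part is listed too: "Facilities and individuals will be modelled as random effects with remaining variables modelled as fixed effects". Organisation is in neither list. The sample size paragraph likewise allows only for clustering within facilities.

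**The concern.** A trial that randomises within blocks normally carries the blocks into the analysis. Here the blocks are organisations, whose facilities share one champion and presumably share management and policy. Whatever they share affects all three conditions in that organisation alike, so it drops out of the true sampling error of a comparison between conditions. A model that stops at facility treats the 39 facilities as independent and counts the shared variation as facility variance. The standard error is then larger than the design warrants.

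At stake is precision in the comparison of the supported programme with usual care at 6 months: wider confidence intervals, a test below its nominal level, and some lost power, although the organisers have already gone to the trouble of finding three facilities per organisation. This cannot be set aside as detail left to a statistical analysis plan, because the article lists the levels, predictors and random effects, and that list does not match its own randomisation.

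**Working it through.** **Inputs from the article (Study design).** 13 organisations with 3 facilities each; d = 0.35 for supported programme versus control at 6 months; two-sided 5%; 80% power; within-facility ICC 0.02; 20 residents per facility; 25% resident and 33% staff attrition.

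**Assumptions, not in the article.** The share s of the ICC that lies between organisations, taken from 0 to 100%; an ICC of 0.05 as a sensitivity case.

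**Step 1: the stated sample size.** Without clustering, n per arm = 2(1.960 + 0.842)²/0.35² = 128.1, so 129. With design effect 1 + (m − 1) × 0.02:
- m = 22: 129 × 1.42 = 183.2; divided by 0.75 this gives 245 residents, and by 0.67, 274 staff.
- m = 23: 129 × 1.44 = 185.8, so 186; this gives 248 residents and 278 staff, exactly as stated.
- m = 20: 129 × 1.38 = 178.0; this gives 238 residents, 4% below the stated 248.

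The stated figures are reproduced without any organisation component.

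**Step 2: standard error of the 6-month difference between two conditions.** With 20 × 0.75 = 15 completers per facility and SD 1:
- organisation omitted: SE² = (2/13)[ICC + (1 − ICC)/15]
- organisation included: SE² = (2/13)[ICC(1 − s) + (1 − ICC)/15]

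At ICC 0.02 and s = 50%: √[(2/13)(0.0200 + 0.0653)] = 0.1146 against √[(2/13)(0.0100 + 0.0653)] = 0.1077. The ratio is 1.064 and the variance falls by 12%.

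**Step 3: type I error and power.** These come from 200,000 simulated trials per row. The model without organisation uses 39 − 3 = 36 degrees of freedom; the model with it uses 36 − 12 = 24.

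| ICC | share s | SE without / with | type I error without / with | power without / with |
|---|---|---|---|---|
| 0.02 | 0% | 0.1146 / 0.1146 | 5.0% / 5.0% | 84.4% / 83.4% |
| 0.02 | 50% | 0.1146 / 0.1077 | 3.8% / 5.0% | 85.9% / 87.7% |
| 0.02 | 100% | 0.1146 / 0.1003 | 2.7% / 5.1% | 87.3% / 91.7% |
| 0.05 | 50% | 0.1320 / 0.1166 | 2.8% / 4.9% | 75.8% / 82.2% |

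The normal approximation to the type I error without organisation, 2[1 − Φ(1.96 × SE ratio)], gives 3.7% at s = 50% and 2.5% at s = 100% for ICC 0.02, in line with the simulation.

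Power without organisation is the actual rejection rate: the estimate has the smaller blocked variance, while the test uses the larger unblocked standard error. This is why it rises with s although the reported standard error does not.

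**Step 4: change from baseline.** Generalised least squares was applied to the article's three-level structure: 13 × 3 facilities, 20 residents each, four time points, 25% lost by 6 months, an assumed within-person correlation of 0.6, and half the ICC at organisation level. The standard error of the Condition-by-time contrast from baseline to 6 months is 0.087 without an organisation intercept and 0.087 with it. A constant organisation effect cancels, just as the facility intercept does.

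**The case against.** The strongest objection is that the losses above belong to a contrast that the article does not clearly test. The model contains a Condition-by-time interaction, and the Hypotheses section predicts changes relative to baseline. If that interaction is the test, Step 4 shows nothing to gain from an organisation intercept. This stands and limits the point. It does not remove it: the same section makes quality of life at 6 months the primary outcome, the sample size rests on the difference between conditions at that time, and the Statistical analysis section speaks of testing main effects. Organisations may also differ in change over time, which is plausible with one champion each, and that variation would matter for the interaction.

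Second, the article gives no organisation variance. At the planned ICC the gain is small, and if organisations do not differ, adding them costs about 1 point of power. This also stands. The larger gain at ICC 0.05 needs 2.5 times the planned value.

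Third, nothing in the article forbids adding organisation as a design covariate in a fuller plan. That is true, but the terms are listed and it is not among them.

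A reader might infer that the analysis is invalid or that the benefit of blocking is lost altogether. The documents do not support that. The balance from allocating within organisations is kept whatever model is fitted, the estimate is unbiased, and the error runs only towards caution.

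**Conclusion.** The mismatch is real: randomisation is within organisation and the specified model ignores organisation. Its effect is confined to precision. For the 6-month comparison between conditions at ICC 0.02, the standard error is 0 to 14% too large, the type I error is 5% down to about 2.6%, and adding organisation changes power by about -1 to +4 points. The result rests on one facility per condition in each organisation (implied, not written), 15 completers per facility, and an assumed organisation share of 0 to 100%.

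A reader might infer that the trial is underpowered as planned. At the planned ICC, power exceeds 80% with or without organisation. Only at a higher ICC, such as 0.05 with half of it between organisations, does the omission make the difference between about 76% and 82%. Nor do the documents show that the loss is larger for staff climate or leadership measures; that is plausible, but no figure supports it. For a change-from-baseline test the intercept makes no difference, and only organisation-by-time variation would count.

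**What to change.** State in the Study design section that allocation is one facility per condition within each organisation. In the Statistical analysis section, add organisation to every model, either as 12 fixed block effects or as a fourth-level random effect above facility. Say whether the primary test is the 6-month difference between conditions or the change from baseline; if change is tested, add an organisation-by-time term, because a main effect alone would do nothing there. Use small-sample degrees of freedom, about 24 for the facility-level contrast.

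The cost is a few sentences and no extra participants. Fixed block effects use 12 degrees of freedom, about 1 point of power if organisations do not differ (84.4% to 83.4% at ICC 0.02). Settling this before the data are seen also keeps the choice of model from depending on the results.

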**Fig. 1 Fig1:**
[figure not shown]
Flow chart of staff recruitment, baseline, roll out of the program, post-intervention and follow-up

A 0.5 FTE study champion appointment will be made by each organization. This study champion will be recruited from the commencement of the study, with a brief to work with staff and the research team to assist in the roll out of the strategies identified as a result of the training program. This study champion will assist in the recruitment of staff and residents for the study as well as assist staff to embed the strategies from the program into routine practice. The study champion will be an important link between the staff in the two intervention facilities and the research team implementing the protocol. In addition to the organizational support provided for Condition 1, the study champion will assist staff to overcome barriers to CDC implementation throughout the 15 months of the study period. The overall study will run from January 2018 through to December 2020. The first round of staff and resident recruitment and data collection commenced in May 2018 and it is anticipated the final round of data collection will be completed by July 2020. The roll-out of the training program will run from June 2018 to July 2019. The second half of 2020 will be dedicated to data analysis and interpretation, and writing of publications.

Informed by the results of our earlier NHMRC-funded RCT (APP1042156) our study is designed to detect a moderately small difference *d* ≥ 0.35 between the RCC plus organizational support and control Condition in QoL of residents at 6-months follow up (primary outcome) and in staff outcomes post-intervention (secondary outcomes). We selected 6-months follow up as our primary endpoint for residents’ QoL because we expect a gradual and continuing change in this outcome as a result of changing practice. Allowing for 80% power, 5% Type I error rate (2-tailed), intra-class correlation of 0.02 for the within-facility clustering, and 25% (residents) and 33% (staff) attrition over time, we will need to randomize at least 744 residents (248 per Condition) and 834 staff (278 per Condition). Based on our previous work in the residential aged care setting, we expect an average recruitment of 20 residents and 22 staff per site. Hence, 39 aged care facilities will need to be enrolled into the study (13 for each arm of the RCT). Data analysis is discussed later in the Methods/Design section.

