#### Transformational leadership

The Multifactor Leadership Questionnaire (MLQ) – Leader version by Bass and Avolio [25] will be used to assess the senior staff’s perception of their own leadership style. The scale consists of 45 items in 9 subscales that can be condensed into 4 subscales. Responses are recorded on a 5-point scale, with higher scores on each subscale indicating the extent to which a staff member employs a particular leadership style. The scale has demonstrated good reliability, with the alpha for the subscales ranging from .61 to .91 [25].

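### The 80% power claimed for staff outcomes does not hold for transformational leadership, which only the senior half of staff report: about 58–62% at d = 0.35

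*Protocol article*

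**What the plan says.** The Study design section says the trial should be able to "detect a moderately small difference *d* ≥ 0.35 between the RCC plus organizational support and control Condition", and applies this target to differences "in QoL of residents at 6-months follow up (primary outcome) and in staff outcomes post-intervention (secondary outcomes"). The inputs are a power of 80% with a two-sided 5% test, an "intra-class correlation of 0.02 for the within-facility clustering", and expected losses of 25% for residents and 33% for staff. For staff, the result is "834 staff (278 per Condition"), with 22 staff expected per site and 13 facilities per arm. No staff outcome is excepted.

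The Abstract lists transformational leadership among the secondary outcomes reported by staff, and the hypotheses section predicts that it will improve. Under Transformational leadership, the instrument is the leader version of the Multifactor Leadership Questionnaire, used to assess senior staff's "perception of their own leadership style". The Abstract gives the staff sample as "834 staff (22 in each facility, half senior, half general staff"), and the Participants section likewise plans approximately equal numbers of the two groups.

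**The concern.** The power statement treats every staff outcome as if all 278 staff per condition contributed data. For transformational leadership only the senior half do, so the stated sample size does not apply to this outcome.

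The Background presents this leadership style as central to turning the training into practice, and names it first among the critical factors the program addresses. If no difference were found, a reader relying on the sample-size paragraph would think the trial had an 80% chance of detecting d = 0.35. In fact it would miss a true effect of that size about 40% of the time, twice the stated 20%.

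**Working it through.** **Inputs, all from the protocol.** d = 0.35 (SD = 1), two-sided α = 0.05, ICC = 0.02, staff attrition 33%, 278 staff per condition, 22 staff recruited per facility, 13 facilities per arm, half of staff senior.

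**Formulas.** Design effect DE = 1 + (m − 1) × ICC, where m is the number of staff per facility. SE = √(2 × DE / n), where n is the number analysed per arm. Power (normal) ≈ Φ(d/SE − 1.96). Detectable d at 80% power = (1.96 + 0.842) × SE.

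**Step 1: reproduce the stated figure.**
- Two means at d = 0.35 need 129 per arm (130 with the t-distribution).
- With m = 22, DE = 1 + 21 × 0.02 = 1.42.
- 129 × 1.42 / 0.67 = 274 per arm (276 with the t-distribution; 277 if attrition is also taken as one third). The protocol states 278.
- Using the post-attrition cluster size in the design effect gives only 246–249, so the protocol evidently used the recruited cluster size of 22.
- Power with all staff: n = 278 × 0.67 = 186.3; SE = √(2 × 1.42 / 186.3) = 0.1235; 0.35 / 0.1235 = 2.83; power 80.9%.

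The arithmetic behind 278 is therefore sound when all staff contribute.

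**Step 2: senior staff only.** 278 / 2 = 139 per condition, and 139 × 0.67 = 93.1 analysed.

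| Convention | m | DE | SE | d/SE | Power (normal) | Detectable d at 80% |
|---|---|---|---|---|---|---|
| Protocol's own (recruited cluster size) | 11 | 1.20 | 0.161 | 2.18 | 58.7% | 0.45 |
| Post-attrition cluster size (93.1 / 13) | 7.16 | 1.123 | 0.155 | 2.25 | 61.5% | 0.44 |

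With a t-test on 2 × (13 − 1) = 24 degrees of freedom, the second row gives 58.0% power and a detectable d of about 0.45; the first row gives 55.3%. The lower design effect of the smaller clusters is already credited: power falls less than halving the sample alone would suggest.

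The post-attrition convention applied to all staff (m = 14.3, DE = 1.267) gives 85.1% (normal) or 82.1% (t, 24 df). The 80% claim therefore holds for outcomes measured in everyone under that convention too.

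**Step 3: sensitivity.**
- No attrition: n = 139, m = 10.69, DE = 1.194, SE = 0.131. Power is 76.1% (normal) or 72.7% (t, 24 df); detectable d is 0.37–0.38.
- Exactly 11 senior staff per facility (143 per arm, 95.8 after attrition): 62.6% (normal).
- ICC of 0.05 (an assumption): about 50–55% (normal).
- Needed for 80% power at d = 0.35: 129 × 1.127 / 0.67 = 217 (m = 11 × 0.67 = 7.37) to 129 × 1.20 / 0.67 = 231 (m = 11) senior staff per condition before attrition, against about 139 planned.

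**The case against.** Four points can be made for the protocol.

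**The number itself is right.** The 278 follows from its inputs, and the other scaled staff measures are described as completed by care staff generally, so the claim is sound for those. This stands. The fault lies in applying the figure to an outcome whose respondents are half the sample.

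**The attrition may be too harsh.** The 33% is loss over time, with follow-up to 12 months, whereas the staff target is post-intervention. The protocol gives no separate figure for that point. If loss were 20%, n = 111.2, DE = 1.151, SE = 0.144 and power 68%. If it were 10%, n = 125.1, DE = 1.173, SE = 0.137 and power 72%. Both loss rates are assumptions. The size of the gap depends on attrition, but the gap remains even at zero loss.

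**The planned model could do better.** The analysis is a three-level repeated-measures model, not a comparison at one time point. If baseline were used as a covariate with an assumed correlation of 0.5, the effective sample rises by 1 / (1 − 0.25) and power reaches 74% at 33% loss, or 80–84% at 20–10% loss. A correlation of 0.6 gives about 80% at 33% loss. Counting all 39 facilities (36 df) gives 59% rather than 58%. These are fair possibilities, but the protocol states no correlation, and its own 278 takes no credit for one.

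**It is one secondary outcome.** True: the primary outcome is untouched, and no formal test of mechanism is described. An article may also leave outcome-by-outcome power to a fuller document. Here, however, the article itself makes the claim for staff outcomes without exception, and its own measurement plan contradicts it for a named one.

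**Conclusion.** The concern holds. On the protocol's own inputs, power for transformational leadership at d = 0.35 is about 58–62%, not 80%, and the effect detectable with 80% power is about d = 0.44–0.45. The range covers the choice of cluster size in the design effect and of a normal or t reference. Combining the protocol's cluster-size convention with the t-test on 24 df would take power down to 55%.

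The result assumes an equal split of senior and general staff, ICC 0.02, 33% attrition and an unadjusted comparison of two means, as in the protocol's own calculation. Lower attrition narrows the gap without closing it (73–76% at zero loss). Only a baseline correlation that the protocol does not state could restore 80%. Power for resident quality of life, and for outcomes measured in all staff, is unaffected. The statement should be corrected, but it does not threaten the trial's main conclusion.

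**What to change.** In the sample-size paragraph, limit the claim: 80% power at d = 0.35 applies to staff outcomes measured in all staff. Add that transformational leadership is measured in senior staff only (about 139 per condition), and that under the planned 33% attrition and ICC of 0.02, power at d = 0.35 is about 60% and the detectable effect at 80% power is about d = 0.45. State that this outcome will be interpreted by its estimate and confidence interval, so that a non-significant result is not read as evidence of no effect. If the sponsor expects lower attrition at the post-intervention assessment, or a gain from baseline adjustment, that assumption and the resulting figure should be stated.

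The cost is wording only. One stated figure becomes less favourable; recruitment, design and the primary analysis do not change.
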